### Secondary outcomes

#### Cardiometabolic biomarkers

Blood samples will be taken at baseline and at 12 months follow-up. If patients opt-out of blood collection, blood samples collected in the previous month for usual care purposes will be recorded if available. Patients will be asked to fast for at least 8 h prior to blood collection. The samples will be centrifuged, and the following markers will be analysed: fasting plasma glucose, serum fasting insulin, hemoglobin A1C (HbA1C), serum lipids (triglycerides, total cholesterol, high-density lipoprotein cholesterol (HDL) and low-density lipoprotein cholesterol (LDL)), serum liver function enzymes (gamma-glutamyl transferase (GGT), alanine aminotransferase (ALT), aspartate aminotransferase (AST)), and kidney function (serum creatinine and estimated glomerular filtration rate).

Biomarkers will be used to calculate a bio-medical cardiometabolic risk score, using variables with strong associations to incident cardiovascular and metabolic disease [52]. The cardiometabolic risk score will be calculated as follows: (mean of *z*-scores for fasting glucose, fasting insulin, HbA1c, total cholesterol, (−)HDL cholesterol, triglyceride, ALT, AST, GGT, systolic blood pressure and diastolic blood pressure) × 10. If laboratory values deviate from hospital reference ranges or the Dutch College of General Practitioners’ (NHG) practice guidelines [53–56], the referring healthcare worker (department of internal medicine) or general practitioner (department of orthopedics) will be informed for further action. This will be documented as an adverse event (AE).

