### Participants

Patients with (an increased risk for) cardiovascular disorders (i.e. cardiovascular disease, hypertension, high cholesterol, diabetes mellitus I and II) or with musculoskeletal disorders (i.e. osteoarthritis, total knee or hip prosthesis) aged ≥18 years are eligible for inclusion. Further inclusion criteria are (1) having a body mass index (BMI) of ≥ 25 kg/m^2^ and/or (2) smoking. Patients will be excluded if they are not able to walk at least 100 m safely (e.g. wheelchair-bound), are pregnant, are cognitively unable to comply with a healthy lifestyle intervention referral or to complete study measurements or are not able to communicate in the Dutch or English language.

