### Recruitment and screening

Ongoing recruitment is planned between April 2022 and March 2023. Health care professionals in the hospital will be informed about the LFO and the study during regular meetings, flyers, pocket cards with information about the LFO and a website. Each participating department has a spokesperson (i.e. a local champion) who is tasked with bringing the LFO to the attention of his or her colleagues. Attention for the LFO is also created by the lifestyle broker during multiple disciplinary consultation meetings. Patients will be primarily informed about the study purpose by their health care professional, but also through flyers, narrowcasting in the waiting room and a website (www.lofitleefstijlloket.nl). Health care professionals can refer patients through the electronic patient file system. Subsequently, patients will receive the study information brochure and have the opportunity to take study participation into consideration and to ask questions about the study to a study staff member.

Patients who are interested in participating will be scheduled for a baseline measurement appointment. At baseline, all participants will be asked to sign an informed consent form by the researchers in which they consent to participate in the study, including the collection of data during study measurements, facultative blood sampling and facultative extraction of relevant data from medical records. Participants may additionally consent to an audio recording of the session with the lifestyle broker (in case of randomization to the intervention group). In- and exclusion criteria will be checked during the baseline measurement. Study participation is voluntary, and participants can withdraw from the study at any time without giving any reason and without affecting usual care. Patients’ privacy and data are protected, and all data will be processed after pseudonymization, adhering to standard procedures of the participating medical centres. A screening log will contain all patients screened for the study and the reason why they were excluded from randomization or why they were unwilling to participate, if applicable, to allow the consort diagram to be completed.

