### Data analysis

#### Effectiveness analyses

Data analyses will be conducted after completion of the data collection at 12 months for both parallel randomized controlled trials separately, no interim analyses are planned. Multilevel linear regression analyses will be performed according the intention-to-treat principle with the adapted Fuster-BEWAT at 12 months as the dependent variable, while study group allocation (i.e. intervention versus usual care) and baseline value of the primary outcome will be modelled as independent variables. Multilevel is chosen to account for clustering of patients on the hospital level. Secondary outcomes will be analysed in a similar way using multilevel linear or logistic regression analyses. Analyses will be performed with STATA SE14. Statistical significance will be set at *p*<0.05.The patterns and extent of missing data will be examined; in case it is necessary, multiple imputations methods will be implemented for primary and secondary outcomes, assuming data are missing at random.

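### The cardiometabolic risk score is fixed with a fasting insulin term although insulin users are eligible, and the usual-care blood fallback carries no fasting condition

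*Protocol article*

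**What the plan says.** All references are to the Protocol article.

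- **Score.** Cardiometabolic biomarkers gives an explicit formula: the mean of eleven z-scores, multiplied by ten. The terms are "fasting glucose, fasting insulin, HbA1c, total cholesterol", HDL cholesterol with reversed sign, triglyceride, ALT, AST, GGT, and systolic and diastolic blood pressure. It names no transformation and no reference mean or SD, and has no rule for insulin users.
- **Population.** Participants lists as cardiovascular entry diagnoses "cardiovascular disease, hypertension, high cholesterol, diabetes mellitus I and II". The exclusions begin "Patients will be excluded if they are not able to walk at least 100 m safely" and go on to pregnancy, cognition and language. Insulin treatment is not among them.
- **Blood.** Recruitment and screening makes consent cover "facultative blood sampling and facultative extraction of relevant data from medical records". Cardiometabolic biomarkers then states "Patients will be asked to fast for at least 8 h prior to blood collection", but for those who opt out, "blood samples collected in the previous month for usual care purposes will be recorded if available". No fasting condition is attached to those samples.
- **Analysis.** Effectiveness analyses states "Secondary outcomes will be analysed in a similar way using multilevel linear or logistic regression analyses". The primary model includes the baseline value. Analysis is done "for both parallel randomized controlled trials separately, no interim analyses are planned".

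**The concern.** The formula treats higher insulin as higher risk for everyone. In a patient who uses insulin, the measured value depends partly on the treatment (how far depends on product and assay), so the term need not point in the direction the formula assumes. A change in insulin treatment would also move it, whatever happened to risk. Background hypothesises that the intervention will reduce prescribed medication, so insulin use could come to differ between arms during follow-up. Baseline balance would not remove that.

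The fasting gap is of the same kind. The score is defined on fasting glucose and insulin, and triglyceride also depends on fasting. A sample taken for usual care need not have been fasting. Opting out at 12 months happens after participants know their allocation, so use of the fallback could differ by arm. The document does not allow one to say whether it will.

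At stake is the interpretation of the trial's only composite of blood markers. It is a secondary outcome.

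**Working it through.** The document gives no figure for this score: no SD, no target difference, no marker distributions and no share of insulin users. The sample size of 138 per arm concerns the primary outcome and does not bear on the point. The weights below are exact. Everything else rests on stated assumptions.

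**1. Weights.** Eleven equally weighted terms give each 1/11 = 9.1%. Glucose, insulin and triglyceride together carry 3/11 = 27%.

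**2. What one extreme insulin value does.** With pairwise correlation ρ between terms, the SD of the score is 10·√((1 + 10ρ)/11). An insulin value at z moves that patient's score by 10z/11.

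| ρ (assumed) | SD of score | z = 5: 4.55 points, in SD | z = 10: 9.09 points, in SD |
|---|---|---|---|
| 0 | 3.02 | 1.51 | 3.02 |
| 0.2 | 5.22 | 0.87 | 1.74 |
| 0.4 | 6.74 | 0.67 | 1.35 |

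For group means, suppose the average insulin term differed between arms by one full SD. The mean score would then differ by 10/11 = 0.91 points, which is 0.91/3.02 = 0.30 SD at ρ = 0 and 0.91/6.74 = 0.13 SD at ρ = 0.4.

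**3. What insulin users do to the whole score.** Simulation with 220 patients (about 80% of 276), log-normal markers, log-SD of insulin 0.7, and 0, 10% or 30% insulin users. Their insulin was raised 3- or 10-fold, with extra log-scale spread of 0.8. The last three columns give the correlation with the undistorted score.

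| ρ | Untransformed, no users | Untransformed, 10–30% users | Log scale, 10–30% users |
|---|---|---|---|
| 0 | 0.962 | 0.903–0.926 | 0.955–0.986 |
| 0.2 | 0.984 | 0.964–0.971 | 0.985–0.996 |
| 0.4 | 0.984 | 0.974–0.978 | 0.991–0.997 |

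On the untransformed scale insulin supplies about 4–9% of the score's variance throughout. The largest insulin z-score falls from about 5.8–9.9 untransformed to 3.0–4.1 after logs. The largest shift in any one patient falls from about 0.8–2.9 SD of the score to 0.4–1.2 SD.

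**4. What skew costs if no transformation is used.** The quantity is the standardised effect of the untransformed composite divided by that of the composite with insulin, triglycerides, ALT, AST and GGT on the log scale.

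- Only those five markers fall, by 15% each (log-SD 0.6–0.8, ρ 0–0.4): 0.78–0.87.
- All eleven terms shift by the same standardised amount (log-SD 0.6–1.0, ρ 0 or 0.3): 0.86–0.95.

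Across choices of which markers move and how they correlate, the composite keeps roughly 80–99% of the log-scale effect at log-SD 0.6–0.8. Required sample size scales with one over the ratio squared: 1/0.80² = 1.56 at the low end and 1/0.99² = 1.02 at the high end.

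**The case against.** Several stronger readings are tempting, and the document does not support them.

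- **That insulin drives the score.** Equal weighting rules this out. It is one term in eleven, at about 4–9% of the variance under the assumptions above.
- **That usual-care blood is accepted as fasting.** The text says only that such values are recorded. It neither puts them into the score nor keeps them out. What can be said is that no fasting condition is attached.
- **That the z-scores are raw.** This would be read from silence. Transformation and the standardisation reference may properly sit in an analysis plan that is not shown. The skew calculation therefore supports a recommendation and does not show an error.
- **That skew cripples the score.** For a single log-normal marker, the top 5% of patients do supply 52–63% of the squared z-score (log-SD 0.6–0.8), and a 15% fall keeps only 70–84% of its standardised effect (log-SD 0.6–1.0). Those figures describe one marker. In the composite the top 5% supply about 27–32% of the variance, against 22% for a normal variable.
- **That the comparison is biased.** Randomisation balances baseline insulin use in expectation, and the baseline value enters the model. The main effect is noise.

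It also counts against the point that type 1 diabetes is an entry diagnosis in the cardiovascular trial only, that the trials are analysed separately, and that Table 1 lists the individual markers as outcomes in their own right.

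All of this limits the size of the point without removing it. The article fixes the formula and the eligible population, and the two do not fit for insulin users. The fasting definition and the fallback samples are not reconciled either.

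**Conclusion.** The point holds as a minor one. Followed as written, the insulin term does not measure risk in insulin-treated patients, and up to three of eleven terms may come from non-fasting blood. The consequence is reduced validity and some loss of precision in one secondary score, chiefly in the cardiovascular trial for insulin and in either trial for the fallback samples. Bias would arise only if insulin use or use of the fallback diverged by arm after randomisation. That is possible given the stated hypothesis about medication, but its size cannot be estimated from the document. The primary outcome uses no blood sample, so its conclusion is unaffected.

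The weights follow from the formula. The variance share, correlations and effect ratios rest on assumed log-normal markers, an assumed correlation of 0–0.4 and an assumed 10–30% of insulin users.

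**What to change.** Amend the analysis wording only.

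1. In the cardiovascular trial, compute the score without the insulin term for participants using insulin at baseline, in the same way at both visits. Alternatively, drop the insulin term for all participants as a sensitivity analysis, which also covers those who start or stop insulin later. Table 1 already schedules medication use at baseline. The rule should not depend on insulin use at 12 months, because the intervention may alter it.
2. Let glucose, insulin and triglyceride from usual-care samples enter the score only when fasting is documented, and otherwise treat them as missing.
3. State that insulin, triglycerides, ALT, AST and GGT are log-transformed, and that both visits are standardised to the baseline mean and SD. If an analysis plan already says so, a reference suffices.

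The cost is that some component values become missing and that the score rests on a different number of terms in different patients, which the report should state. No extra measurement and no change to patient care is involved.

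### The article's only adverse event rule counts every out-of-range laboratory value, with no exclusion for baseline samples or for the diseases that make patients eligible

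*Protocol article*

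**What the plan says.** The rule stands in the Protocol article under Secondary outcomes, Cardiometabolic biomarkers. Its trigger is "If laboratory values deviate from hospital reference ranges or the Dutch College of General Practitioners’ (NHG) practice guidelines". The referring health care worker or the general practitioner is then informed, and the text adds: "This will be documented as an adverse event (AE".

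The same section fixes when values arise: "Blood samples will be taken at baseline and at 12 months follow-up". For patients who decline study sampling, "blood samples collected in the previous month for usual care purposes will be recorded if available". The panel covers "fasting plasma glucose, serum fasting insulin, hemoglobin A1C (HbA1C), serum lipids", liver enzymes and kidney function.

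Under Participants, the qualifying cardiovascular conditions are listed as "cardiovascular disease, hypertension, high cholesterol, diabetes mellitus I and II".

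Apart from the abbreviation list, adverse events are mentioned nowhere else in the article.

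**The concern.** The trigger depends only on whether a value is out of range. It does not ask at which visit the value was obtained, whether it is new, whether it is worse than before, or whether it belongs to a known condition. A patient referred with diabetes who has a raised HbA1c at the baseline visit meets the rule before randomized care has started. If the value is unchanged at 12 months, the patient meets it again.

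An adverse event record is useful when it separates what arose during the trial from what the patient brought into it. This rule does not make that separation, and it is the only adverse event rule that the article states. What is at stake is the meaning of any count taken from the record.

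**Working it through.** **The text, taken in order**

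1. *Timing.* Under Recruitment and screening, consent is signed and eligibility checked at the baseline measurement. Under Intervention, the session with the lifestyle broker is scheduled after randomization. A baseline laboratory value therefore cannot be a consequence of the intervention.
2. *Usual-care samples.* The substitute sample for patients who opt out may be up to a month old. At baseline it can predate consent, and the rule does not exclude it.
3. *Overlap with eligibility.* Glucose, HbA1c and lipids are on the panel, and diabetes and high cholesterol are reasons for enrolment. The qualifying condition can itself be recorded as the event.
4. *Repetition.* A stable abnormality meets the trigger at baseline and again at 12 months, so it can be recorded twice.
5. *Other passages.* No other section of the article narrows the rule.

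**Scale (illustration only)**

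The plan gives no figure on this point and no abnormality rates, so there is none to reproduce. Inputs:

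- Markers: glucose, insulin, HbA1c, triglycerides, total cholesterol, HDL, LDL, GGT, ALT, AST, creatinine and eGFR, which makes 12 (Cardiometabolic biomarkers).
- Patients per trial: 2 × 138 = 276 (Sample size and power calculation).
- Assumption, not in the article: each reference range covers the central 95% of healthy people.
- Assumption, not in the article: everyone gives blood (relaxed below).

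With independent markers, the chance of at least one flag at a visit is 1 − 0.95^12 = 0.46, and 0.46 × 276 gives about 127 patients. The markers are clearly correlated (creatinine with eGFR, total with LDL cholesterol, the liver enzymes with each other), so I repeated the calculation for 12 normal variables with equal pairwise correlation:

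| Correlation | Healthy people with at least one flag per visit | Of 276 |
|---|---|---|
| 0 | 46% | 127 |
| 0.3 | 40% | 110 |
| 0.5 | 32% | 88 |
| 0.7 | 23% | 64 |

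These count patients. If each value is counted as its own event, the expected number is 12 × 0.05 = 0.6 per healthy person per visit whatever the correlation, or 0.6 × 276 ≈ 166.

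The informed-consent text makes blood collection optional ("facultative blood sampling and facultative extraction of relevant data from medical records"), so all counts shrink in proportion to uptake. At an assumed uptake of 50%, for example, 64 to 127 patients becomes 32 to about 63.

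The table describes chance flags in healthy people. It does not measure the contribution of pre-existing disease, for which the article supplies no input.

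**The case against.** The strongest reply is that little depends on this record. Adverse events are not an outcome in Table 1, and the Effectiveness analyses section plans no adverse event table and no comparison between arms. The same markers are secondary outcomes, analysed like the primary outcome with group and baseline value in the model, so laboratory deterioration by arm is examined directly. Randomization should balance pre-existing abnormalities on average. All of this stands, and it limits the point.

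A reader might infer that new abnormalities are buried or that the trial loses its ability to detect harm. The documents do not support that: over-recording removes no data, and out-of-range values are still passed on to the treating professional. A reader might also suppose that nearly all patients with diabetes or high cholesterol would be flagged. No figure in the article supports that either; treated patients may be in range, and the guideline thresholds are not given.

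A second reply is that a condensed article leaves adverse event detail to the full protocol. That would answer a complaint about missing severity or causality rules. It does not answer a rule that is stated positively and without exception. If the full protocol contains an exemption, the article misreports the rule.

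A third reply is that the word *This* may refer to the notification and not to each value. Since every deviation triggers notification, that changes the counting unit but not which patients are recorded.

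**Conclusion.** The point holds as a small correction to the adverse event record. Read literally, the rule mixes disease present before the intervention with events arising during the trial, so a count drawn from it would be inflated in both arms and hard to interpret. The primary outcome, its sample size and the baseline-adjusted biomarker analyses are untouched.

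The conclusion rests on the wording of the rule together with the sampling times and the eligibility list. It does not depend on the illustrative percentages, which require 95% reference ranges and, for the patient counts, full uptake of optional sampling. The excess due to pre-existing disease cannot be sized from the article.

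**What to change.** Amend the rule in the Cardiometabolic biomarkers section as follows:

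- Record out-of-range baseline results, and usual-care results from before consent, as pre-existing findings and not as adverse events.
- At 12 months, document an adverse event only when a value is newly out of range or has worsened from the patient's own baseline by a margin or grade set in advance. Without a margin, ordinary measurement variation would make many stable abnormal values count as worse.
- If adverse events are reported, give them by arm among patients with both samples.
- Leave the notification of the treating professional as it is.

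The cost is a short change to the protocol text, a baseline-comparison check in the case report form, and the work of setting the margin in advance. The values needed are already collected at both visits. The restriction to patients with both samples leaves out those who gave only one, so their number should be stated.

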#### Anthropometric measures

The following anthropometric measures will be carried out. Body height will be measured to the nearest centimetre at baseline only with a stadiometer (SECA 206, SECA, Birmingham, UK). Body weight to the nearest 0.1kg without shoes and light clothes will be measured using calibrated electronic scales (SECA 877). Body height and weight will be used to calculate BMI (kg/m^2^). BMI (i.e. categorized into >31.9 (0); 30–31.9 (1); 27–29.9 (2); 25–26.9 (3); <25 (4)) will be used for the adapted Fuster-BEWAT score. Waist circumference will be measured twice to the nearest 0.1 cm with a SECA 201 measure (no shirt on), midway between the lowest ribcage and the iliac crest. If the difference between the two measures is >0.5 cm, a 3rd measurement will be conducted. The mean will be calculated from the two nearest measurements. Body height and waist circumference will be used to calculate the waist-to-height ratio [57]. Neck circumference will be measured once to the nearest 0.1cm with a SECA 201 measure in a standing relaxed upright position between the mid-cervical spine and mid-anterior neck [58]. For resting blood pressure, Omron M6 blood pressure monitor was used after 5 min of sitting still. If measured systolic blood pressure is >139 mmHg and/or measured diastolic blood pressure is >89 mmHg, two additional measurements will be taken and recorded. A mean will be calculated from the second and third measurements. Both systolic and diastolic blood pressure (i.e. categorized into systolic/diastolic: >140/90 (0); 134–139/87–89 (1); 128–133/84–86 (2); 121–127/81–83 (3); <121/81 (4)) will be used for the adapted Fuster-BEWAT score. All equipment used in the different hospitals is identical.

